### Treatment of patients

Details of the drug combinations and duration for each of the Regimens A-D are shown in Table 1. Table 2 provides details on the drug types and dosages included in each regimen. In case of grade 3 or 4 AE triggered by Lzd, the Lzd dose was cut to 300 mg or ceased entirely as required. The rest of the five drugs, Bdq included, were given throughout the course of the treatment. All medications used in the study have received approval from the National Medical Products Administration and are prescribed solely by authorized study physicians at the respective research sites. None of the medications are provided free of charge. Contrary to employing the Directly Observed Treatment (DOT) strategy, this study designates a clinic staff member to oversee each patient’s treatment. This individual is tasked with verifying medication consumption, documenting it on the treatment card, and providing guidance to ensure proper administration and patient adherence.

**Table 2 Tab2:** Trial regimen drugs and doses

Drug	Weight group		Usage
	≤ 50 kg	> 50 kg	
Bedaquiline	400 mg daily for 2 weeks followed by 200 mg three times a week		Once, with meal
Linezolid	600 mg daily		Once, before or after meal
Moxifloxacin	400 mg daily		Once, before or after meal
Levofloxacin	500 mg daily	750 mg daily	Once, before or after meal
Cycloserine	500 mg daily	750 mg daily	Divided in two doses, before or after meal
Clofazimine	100 mg daily		Once, with meal
Pyrazinamide	1500 mg daily		Once, before or after meal
Sulfasalazine	3000 mg daily		Divided in three doses, with meal

Based on our prior cohort study experience and international guidelines, we have formulated a manual for the management of adverse reactions to second-line anti-TB drugs for the SEAL-MDR study (Table S5). Management of treatment interruptions was shown in Table S6.

### Outcome measures

In this study, outcomes are categorized at the end of a 12-month post-treatment follow-up. Participants fall into one of three categories: unfavorable outcome, favorable outcome, or not assessable - the latter are excluded from the primary analysis (Table S7). The primary efficacy outcome, determined 15 months after initial assignment, includes treatment failure, loss to follow-up, or death from any cause. Treatment failure is a multifaceted term, defined by the end-point review committee, and encompasses lack of clinical and/or bacteriological response, adverse drug reactions that induced regimen adjustments, or newly identified drug resistance. Specifically, bacteriologic failure is defined by the presence of two genetically identical, *M. tuberculosis*-culture-positive sputum samples within the month 8 visit window. Bacteriologic relapse and reinfection refer to a positive test for a genetically identical or different *M. tuberculosis* strain, respectively, within 12 months post-treatment. In cases where strain genotyping is not feasible, the term ‘bacteriologic recurrence’ is employed. Secondary efficacy outcomes include unfavorable status at 21 months post-assignment, end-of-treatment success, culture conversion by month 2, time to sputum culture-negative status in liquid media, and favorable treatment response at FR-6. Safety outcomes involve the occurrence of AEs graded ≥ 3 or serious AEs of any grade within 6–9 months of treatment initiation, as per the DAIDS AE Grading Table [15]. Clofazimine-induced skin discoloration is also specifically documented (Table S2).

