**Fig. 1 Fig1:**
[figure not shown]
The flow diagram of the SEAL-MDR study. The diagram outlines the key steps in the study, starting with patient recruitment, followed by initial selection of treatment regimens based on *M. tuberculosis* drug resistance spectrum and patient preferences. For the randomized withdrawal trial, patients with a favorable treatment response will be randomized to 6 or 9 months of treatment after 6 months of treatment. Participants with a poor treatment response will not be randomized but will continue on a 9-month treatment regimen. In the single-arm trial, participants with a favorable response will stop treatment at month 6, otherwise treatment will be extended to 9 months. Throughout the study, FQ resistance results may be obtained at various stages to guide initial and subsequent regimen adjustments. Participants will attend visits at 12 months post-treatment to obtain primary and secondary endpoints. (Abbreviations in this figure: Bdq: bedaquiline; Cfz: clofazimine; DST: Drug susceptibility testing; FQ: fluoroquinolone; Lzd: linezolid; Mfx: moxifloxacin; Pza: Pyrazinamide; Rif: rifampicin; SASP: Sulfasalazine; TB: tuberculosis)

**Table 1 Tab1:** Trial regimens

FQ susceptibility	Regimen	Drugs	Durations
MDR-TB	A	bedaquiline, linezolid, moxifloxacin, cycloserine and pyrazinamide	6–9 months
	B	linezolid, moxifloxacin, cycloserine, clofazimine and pyrazinamide	6–9 months
Pre-XDR-TB	C	bedaquiline, linezolid, cycloserine, clofazimine and pyrazinamide	6–9 months
	D	linezolid, cycloserine, clofazimine, pyrazinamide and salazosulfapyridine	6–9 months

This study, named SEAL-MDR, was registered with the Chinese Clinical Trials Registry and has received ethical approval from participating hospitals. Written informed consent will be obtained from all adult participants or their legal guardians by trained medical personnel who may be an investigator, clinician, or designated nurse experienced in explaining the elements of clinical trials.

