Participants attend baseline screenings, bi-weekly visits for the first two months, monthly visits until treatment completion, and quarterly check-ups during a 12-month post-treatment period (Tables S3 and S4). The screening procedures include medical history, physical examination, vision tests, peripheral neuropathy screening, psychological assessments, and the collection of various samples for testing. CT scans are preferred over X-rays for assessing lung lesions, which is a routine at the study sites.

Upon passing the screening, eligible participants are enrolled, registered offline, and assigned a treatment regimen by an authorized researcher at each sub-center. These assignments are re-verified by the Central Coordination and Quality Control Group (CCQCG) at Shenzhen Third People’s Hospital.

Effectiveness and safety metrics are evaluated at each follow-up visit through symptom checklists, clinical exams, and ongoing diagnostic tests. Grade 3 or 4 clinical and laboratory adverse events (AEs) are defined per the DAIDS AE Grading Table [12]. Chest CT scans are regularly updated and reviewed blindly by two independent experts using a standardized approach (Table S2). An endpoint review committee examines unfavorable clinical outcomes like treatment failure, TB recurrence, or death. Adherence metrics and educational counseling are also provided, along with psychological support through WeChat and telephone channels. Post-treatment, successfully treated cases will be monitored for 12 months to assess any TB recurrence.

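### The primary outcome is given two incompatible time points, one of which follows the 9-month arm three months longer after randomisation; the 21-month secondary outcome falls after the 6-month arm's last visit

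*Protocol article*

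**What the plan says.** All references are to the protocol article.

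- **Post-treatment rule.** Outcome measures opens by stating that "outcomes are categorized at the end of a 12-month post-treatment follow-up". It sorts participants into unfavourable, favourable or not assessable, and of the last group says "the latter are excluded from the primary analysis". The Fig. 1 legend agrees: "Participants will attend visits at 12 months post-treatment to obtain primary and secondary endpoints".
- **Fixed-time rule.** The same paragraph continues: "The primary efficacy outcome, determined 15 months after initial assignment". The components listed are treatment failure, loss to follow-up and death from any cause.
- **Later secondary outcome.** "Secondary efficacy outcomes include unfavorable status at 21 months post-assignment".
- **Visit schedule.** Randomization, enrolment and follow-up provides "quarterly check-ups during a 12-month post-treatment period" and adds: "Post-treatment, successfully treated cases will be monitored for 12 months to assess any TB recurrence". No later visit is described.
- **Origin.** Initial assignment is not defined. The same section describes two candidate events: a regimen is assigned at enrolment, and responders are randomised to 6 or 9 months of treatment at the month-6 visit.

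**The concern.** The trial's main claim is that 6 months of treatment is non-inferior to 9. That comparison needs one primary outcome read at one time. Here the outcome, and the not-assessable category that decides who is left out of the primary analysis, are tied to the end of post-treatment follow-up, while the primary outcome is also tied to a fixed time after assignment. Recurrence is named among the unfavourable outcomes that the endpoint review committee examines. A recurrence at month 17 would count under the first rule. It would not count under the second rule if the clock starts at enrolment.

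Two things are at stake. If the rule is settled after outcome data are visible, the choice can affect the conclusion. And the post-treatment rule observes the control arm for longer after randomisation, on a composite that includes death and loss to follow-up. In a non-inferiority comparison, that imbalance leans toward the result the sponsor hopes for.

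**Working it through.** **Inputs.** Arms of 6 and 9 months, randomised at month 6 (Trial design and oversight; Randomization, enrolment and follow-up). Quarterly visits for 12 months after treatment (same section). Assumed favourable rate 73%, FR-6 rate 90%, 1:1 allocation, margin 15 points, 608 participants in Groups A and B (Sample size calculation). I take enrolment and treatment start as the same day.

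**The plan's own figure.** Per arm, 2 × 0.73 × 0.27 × (1.645 + 0.842)² / 0.15² gives 109 after rounding up. Two arms make 218, and 218 / 0.90 / 0.80 = 302.8, against the stated 304. The sample size reproduces within rounding. It attaches no time point to the 73%, so it does not settle which rule was meant.

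**Scheduled post-treatment visits (month from treatment start).** 6-month arm: 9, 12, 15, 18. 9-month arm: 12, 15, 18, 21.

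**Where each rule falls (6-month arm / 9-month arm).**

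| Rule | Clock starts at | Month from treatment start | Months since randomisation | Months off treatment | Visit scheduled |
|---|---|---|---|---|---|
| 12 months post-treatment | end of treatment | 18 / 21 | 12 / 15 | 12 / 12 | yes / yes |
| Primary, 15 months | enrolment | 15 / 15 | 9 / 9 | 9 / 6 | yes / yes |
| Primary, 15 months | randomisation | 21 / 21 | 15 / 15 | 15 / 12 | no / yes |
| Secondary, 21 months | enrolment | 21 / 21 | 15 / 15 | 15 / 12 | no / yes |
| Secondary, 21 months | randomisation | 27 / 27 | 21 / 21 | 21 / 18 | no / no |

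With neither origin does the 15-month rule match the post-treatment rule in both arms.

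**Illustration of the post-treatment rule.** Let u be the risk over the 15 months after randomisation, the same in both arms, with constant hazard h = −ln(1 − u)/15. The 6-month arm, read at 12 months, shows 1 − exp(−12h).

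- u = 27% (the complement of 73%): 22.3%, difference 4.7 points.
- u = 19% (1 − 0.73/0.90 = 18.9%, if every participant without FR-6 were unfavourable): 15.5%, difference 3.5 points.
- u = 10%: 8.1%, difference 1.9 points.

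The protocol gives no risk for randomised responders after month 6, so all three values of u are assumptions.

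**Participants without a month-21 visit.** 608 × 0.90 / 2 = 273.6, about 274 planned in the 6-month arms before dropout.

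**The case against.** The best defence is that the fixed-time rule, counted from enrolment, is sound. Month 15 is a scheduled visit in both arms and gives each 9 months since randomisation. That stands. It answers the question of bias for that rule, but not the conflict with the opening sentence of Outcome measures and the Fig. 1 legend. The post-treatment rule also has a rationale: it gives both arms 12 months off treatment in which to relapse. It does so by giving the control three more months at risk of death and loss. Tables S3, S4 and S7 are not shown and may define visit windows, but they cannot make the article's two statements agree.

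Four stronger readings are tempting and are not supported:

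- **That 9 versus 6 months off treatment at a common time is a flaw.** It is inherent in comparing two durations at the same time since randomisation. Month 18 keeps the same three-month gap (12 versus 9).
- **That events from months 0 to 6 materially enter the comparison.** Randomisation requires a favourable response at month 6, and the mITT set contains only randomised participants, so earlier deaths and losses cannot appear. FQ resistance found early moves a participant to Regimens C/D or out of the study. Early regimen changes for adverse reactions could remain, but randomisation balances them in expectation.
- **That the bias is 4.7 points.** That is the top of an assumed range. The 27% applies to Groups A and B before responders are selected, and a constant hazard is doubtful when bacteriological failure is read around month 8. The control's extra months are also on treatment, so some added events could be a real effect of longer treatment.
- **That the 21-month result is missing for the whole 6-month arm.** Events up to month 18 are known there. Only new events in months 18 to 21 go unseen.

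**Conclusion.** The point holds as an internal contradiction about the primary outcome and should be corrected before analysis. The article places the primary outcome at months 18 and 21, and also at month 15 (or month 21 if the clock starts at randomisation). This follows directly from its own statements and needs no statistical assumption.

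The post-treatment rule gives 12 versus 15 months at risk after randomisation. For deaths and losses, the lean toward non-inferiority requires only that some occur in the extra three months. Its size is not known. The range of 1.9 to 4.7 points rests on a constant hazard, equal true risk and assumed 15-month risks of 10% to 27%.

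The 21-month secondary outcome, counted from enrolment, detects new events in months 18 to 21 only in the 9-month arm. Counted from randomisation it is month 27, nine and six months after the last visits of the 6- and 9-month arms. The sample size is not affected.

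**What to change.** 1. Define one time origin in Outcome measures, and score the primary outcome in both arms at the same time since randomisation, at a visit both already attend. Month 15 or month 18 from treatment start would serve (9 or 12 months after randomisation). Month 18 captures more relapse, but it is not the only valid choice.
2. Make and document the choice without sight of outcome data by arm. Recruitment began in April 2021, so this is a dated protocol amendment and more than an editorial correction.
3. Bring the opening sentence of Outcome measures and the Fig. 1 legend into line. Keep the 12-month window ("within 12 months post-treatment") for the relapse and reinfection definition only.
4. For the 21-month secondary outcome, either move it to month 18 or add one month-21 contact in the 6-month arm. If month 18 becomes the primary time point, moving the secondary there merges the two, so keeping a separate later outcome would need the added contact.

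The cost is an amendment to the wording and, if the 21-month outcome is kept, one contact for each of up to about 274 participants. The visits needed for the primary outcome are already scheduled.

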### Randomization, enrolment and follow-up

Before initiating treatment, all available DST results (e.g., Xpert, gDST, pDST) are employed to triage patients with MDR-TB and pre-XDR-TB. Considering variables such as regimen affordability and past adherence, MDR-TB patients are allocated to either Regimen A or B (Table 1). Regimen B is preferred for uninsured participants, those concerned about drug costs, and individuals willing to accept potential skin discoloration caused by Cfz. Pre-XDR-TB patients are allocated to either Regimen C or D, with Regimen D being better suited for those without insurance coverage and lesser financial means.

Should post-entry DST results confirm resistance to any study drug, treatment regimens will be adjusted according to established clinical practice principles in our previous studies [1]. For example, If initial gDST is unavailable and later pDST reveals FQ resistance 2–3 months post-enrollment, participants will transition from Regimens A/B to C/D, incorporating the prior treatment duration into the revised 6-month course. In certain scenarios, participant withdrawal may be necessitated. For example, participants unwilling to switch sill be prescribed long-course treatment and excluded from the study.

Participants initially undergo a 6-month treatment course. A blinded mid-point review committee evaluates clinical events and favorable treatment responses during the sixth-month visit (FR-6, Table S2). This assessment includes sputum culture conversion at month four, adequate drug intake at month six (excluding those who received less than ~ 90% of study doses), and chest computed tomography (CT) stabilization. Participants having a FR-6 will be centrally randomized into either a 6- or 9-month treatment group via MedSci RTSM Cloud Platform (rtsm.medsci.cn). Otherwise, they will continue their current regimen until month nine. Failure to convert by the eighth month necessitates an extension to an 18–20 month regimen, marking it as a treatment failure.

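### Between months 6 and 9 the written bacteriological event definition differs by randomised arm: one positive test off treatment, two genotyped positive cultures on treatment

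*Protocol article*

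**What the plan says.** The Protocol article, Outcome measures, gives two bacteriological definitions that depend on treatment status.

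- **On treatment:** "bacteriologic failure is defined by the presence of two genetically identical, *M. tuberculosis*-culture-positive sputum samples within the month 8 visit window".
- **After treatment:** "Bacteriologic relapse and reinfection refer to a positive test for a genetically identical or different *M. tuberculosis* strain, respectively, within 12 months post-treatment". No second sample is asked for, and the test is not restricted to culture.
- **Without genotyping:** a sentence beginning "In cases where strain genotyping is not feasible, the term" relabels the post-treatment event as recurrence. No such fallback is given for failure.

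The primary outcome is worded: "The primary efficacy outcome, determined 15 months after initial assignment, includes treatment failure, loss to follow-up, or death from any cause". Relapse and recurrence are not in that list. Under Randomization, enrolment and follow-up, however: "An endpoint review committee examines unfavorable clinical outcomes like treatment failure, TB recurrence, or death". Treatment failure itself is wider than bacteriologic failure: "Treatment failure is a multifaceted term, defined by the end-point review committee, and encompasses lack of clinical and/or bacteriological response".

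On design and schedule: "Participants having a FR-6 will be centrally randomized into either a 6- or 9-month treatment group". Visits are "monthly visits until treatment completion, and quarterly check-ups during a 12-month post-treatment period". A favorable response at month 6 requires culture conversion at month four, so a positive culture after randomisation is a reversion.

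**The concern.** Participants are randomised to stop at month 6 or continue to month 9. For those three months, on or off treatment is therefore the same thing as allocated arm, and a definition that depends on treatment status depends on arm.

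The visit schedule sharpens this. After stopping, the 6-month arm is next seen at about month 9 and has no scheduled month 8 visit. The two-culture failure definition can in practice be met only in the 9-month arm, and the one-positive definition at month 9 only in the 6-month arm.

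At stake is the non-inferiority comparison of unfavorable outcomes. Part of any observed difference could come from the measuring rule and not from treatment duration. A one-positive rule after treatment also turns isolated positives (contamination, a transient positive between negatives) into events in the single-arm Groups C and D, whose sample size rests on an assumed 57% favorable rate.

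**Working it through.** **1. The same result in each arm, months 6 to 9**

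| Result | 6-month arm (off treatment) | 9-month arm (on treatment) |
|---|---|---|
| One positive at month 9 | Meets relapse, reinfection or recurrence | Meets no bacteriologic definition |
| Two identical positives in the month 8 window | No visit scheduled in that window | Meets bacteriologic failure |
| Positives at months 7 and 9 | No month 7 visit; the month 9 positive alone suffices | Outside the window; meets no bacteriologic definition |
| Two positives, typing not feasible | Recurrence | No fallback stated; meets no bacteriologic definition |

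The month 9 visit is taken as an on-treatment visit for the 9-month arm. The rule that extends treatment for failure to convert by month eight does not settle these cases, because randomised participants had already converted.

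**2. The plan's own sample size**

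Inputs from Sample size calculation: favorable rate 73%, margin 15 points, one-sided 5%, power 80%, month-6 response 90%, dropout 20%.

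n per arm = 2 × 0.73 × 0.27 × (1.645 + 0.842)² / 0.15² = 108.3, so 109. Two arms give 218, and 218 / 0.9 / 0.8 = 302.8. Rounding dropout up per arm first gives 2 × 137 / 0.9 = 304.4. Both agree with the stated 304. Power with 109 per arm is Φ(0.15/0.0601 − 1.645) = 80%.

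**3. Effect on the randomised comparison**

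The documents give no rate of isolated positives, so I assume q = 0.5%, 1% or 2% per visit. I also assume that each such positive is counted. Only otherwise favorable participants can be reclassified, so the favorable rate after k post-treatment visits is 0.73 × (1 − q)^k. Power is Φ((0.15 − d)/SE − 1.645), where d is the 9-month minus the 6-month favorable rate and SE uses 109 per arm.

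Reading A: 15 months from treatment start. Post-treatment visits fall at months 9, 12 and 15 in the 6-month arm (k = 3) and at 12 and 15 in the 9-month arm (k = 2).

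| q | 6-month arm | 9-month arm | d (points) | Power |
|---|---|---|---|---|
| 0.5% | 71.9% | 72.3% | 0.4 | 78% |
| 1% | 70.8% | 71.5% | 0.7 | 75% |
| 2% | 68.7% | 70.1% | 1.4 | 70% |

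These power figures combine the arm difference with a loss common to both arms. The month 9 visit alone (k = 1 against 0) gives 78%, 76% and 72%.

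Reading B: 12 months after treatment in each arm. Both arms have k = 4, so d = 0. Power is 79%, 78% and 76%, from the common extra events only.

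**4. Groups C and D**

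The plan's figure reproduces: 0.57 × 0.43 × (1.645 + 0.842)² / 0.15² = 67.3, so 68, and 68 / 0.8 = 85. I tested 0.57 × (1 − q)^k against 57 − 15 = 42% with n = 68 (baseline power 80%):

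| k | Power, q = 1% | Power, q = 2% |
|---|---|---|
| 2 | about 75% | about 68% |
| 3 | about 71–72% | about 61–62% |
| 4 | about 68% | about 54% |

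The number of visits depends on when treatment stopped and when the outcome is read. Small differences arise from the variance formula used.

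**The case against.** A reader might infer that the same culture definitely counts in one arm and not in the other. The article does not go that far. Recurrence enters the primary outcome only through the word *includes* and the follow-up section's list of unfavorable outcomes. The endpoint committee defines failure broadly, so a 9-month participant with two untyped positives, or even one positive, can still be ruled a failure. This stands and limits the claim to the written definitions. It does not remove the asymmetry, because no stated rule makes the committee treat an isolated positive alike in both arms.

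Tables S2 and S7 are not shown and may contain confirmation rules. That is a fair caution. The point here, however, is not an absent detail: the article expressly states two different definitions, and further detail in a table would have to reconcile them.

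A reader might also infer that the plan favors a false claim of non-inferiority. The opposite is true, since the extra events fall on the 6-month arm.

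Finally, the four-visit accumulation and the between-arm difference should not be added together. They belong to different readings of the assessment time, and with four visits in each arm the difference vanishes. For Groups C and D, the documents do not give the outcome definition behind the 57% rate. If it already contains isolated positives, the loss is smaller.

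**Conclusion.** The concern holds as a badly fixed outcome rule. As written, the bacteriological definitions differ between the randomised arms in exactly the months in which treatment differs. It matters for the primary comparison if recurrence counts as unfavorable, which is the sensible reading but is not stated in the primary-outcome sentence.

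The size is modest against a 15-point margin. Under Reading A, which takes initial assignment as treatment start (21 months then equals 9 + 12), the difference is about 0.4 to 1.4 points and power about 78% to 70%. Under Reading B the number of single-positive opportunities is equal and the difference is zero, although on-treatment positives in the 9-month arm still lack a matching definition. In Groups C and D only a range is defensible: about 68–75% power at q = 1% and 54–68% at q = 2%.

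All these figures rest on assumed isolated-positive rates and on each such positive surviving committee review. The error is conservative for non-inferiority. Its costs are power and a distorted estimate of the duration effect. The change should be made, because it is cheap and removes an arm-dependent endpoint.

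**What to change.** 1. State in the primary-outcome sentence that recurrence (relapse, reinfection, or untyped) is a component of the unfavorable outcome, if that is intended.
2. Use one bacteriological event definition for both arms, on or off treatment, over the same period counted from randomisation: the same number of positive cultures from separate samples, not confined to the month 8 window.
3. Send a single unconfirmed positive to the endpoint committee, blinded to arm.
4. Use genotyping only to label a confirmed event as relapse or reinfection, and give failure the same fallback where typing is not feasible.
5. Check Tables S2 and S7 against the revised wording, and apply the same definition in Groups C and D.

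The cost is a wording change and an occasional repeat sputum. The downside is that a true recurrence in someone who cannot give a second sample is decided by the committee.

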### Sample size calculation

Group A/B in the randomized withdrawal trial: According to a 2018 IPD meta-analysis [7] and our previous study [14], we assumed that two groups (A and B) have an assumed favorable outcome rate of 73%. Taking into consideration various parameters like a 90% FR-6 rate, a 1:1 random assignment to two different durations (month 6 or month 9), a 15% margin of non-inferiority, a one-sided significance level of 5%, 80% power, and a 20% drop rate, 304 participants are needed for each group. Hence, 304 + 304 = 608 participants in total for groups A and B.

Calculation for Group C/D in the single-arm trial: Two other groups (C and D) have an assumed favorable outcome rate of 57% [7, 14]. Using the same parameters (15% margin of non-inferiority, a one-sided significance level of 5%, 80% power, and a 20% drop rate), 85 participants are needed for each group. Hence, 85 + 85 = 170 participants in total for groups C and D.

Combining both sets of groups, the total sample size required would be 608 + 170 = 778 participants for the SEAL-MDR study.

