### Statistical analysis

Efficacy outcomes will be evaluated using modified intention-to-treat (mITT) and per protocol (PP) approaches, focusing on mITT. The safety analysis includes all participants receiving at least one dose of study drugs. The mITT group consists of those randomized and treated at least once, while the PP group comprises mITT members who complete > 80% of planned treatment and adhere to the protocol.

Analysis is performed in SPSS 26.0. Categorical data are presented as counts and percentages, and continuous data as means (standard deviations, SD) and medians (interquartile range, IQR). Depending on data distribution, Student’s t-test or non-parametric tests are used for continuous variables, and Chi-square or Fisher’s test for categorical ones. Primary analysis estimates unfavorable outcome rates in subgroups of Regimens A and B, with 95% CI for each group. Kaplan-Meier and Cox models evaluate time to unfavorable outcomes and culture conversion. Variables with *P* < 0.1 in univariate analysis and clinical significance are incorporated into a multivariate model. A *P* < 0.05 is considered significant.

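### The only efficacy sets are restricted to randomised participants, so in regimens A and B the secondary outcome FR-6 is 100% by construction, culture conversion is estimated in selected responders, and groups C and D have no efficacy set

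*Protocol article*

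**What the plan says.** The Outcome measures section of the protocol article includes among the secondary efficacy outcomes "culture conversion by month 2, time to sputum culture-negative status in liquid media, and favorable treatment response at FR-6".

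The Statistical analysis section states the populations: "Efficacy outcomes will be evaluated using modified intention-to-treat (mITT) and per protocol (PP) approaches, focusing on mITT". It continues: "The mITT group consists of those randomized and treated at least once". The per-protocol set is drawn from mITT members. The one set that takes in everybody who received a dose is reserved for safety. For conversion the section adds: "Kaplan-Meier and Cox models evaluate time to unfavorable outcomes and culture conversion".

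Entry to randomisation is described under Randomization, enrolment and follow-up: "Participants having a FR-6 will be centrally randomized into either a 6- or 9-month treatment group". On the content of FR-6 the same section says: "This assessment includes sputum culture conversion at month four, adequate drug intake at month six", and it adds stabilisation on chest CT. The Fig. 1 legend confirms the other branch: "Participants with a poor treatment response will not be randomized but will continue on a 9-month treatment regimen".

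Under Trial design and oversight, groups C and D are split between 6 and 9 months by clinical judgment, not by randomisation. The Sample size calculation section plans groups A and B with "a 90% FR-6 rate, a 1:1 random assignment to two different durations (month 6 or month 9), a 15% margin of non-inferiority".

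**The concern.** An outcome that decides who enters an analysis set cannot be estimated in that set. FR-6 is the gate to randomisation in A and B, and the efficacy sets contain only people who passed the gate. The reported FR-6 rate would carry no information about the regimens.

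The two culture-conversion outcomes have a milder form of the same problem. Because conversion at month four is part of FR-6, everyone in the mITT set has converted by then. Participants who convert later, or never, are left out, and so are those who die, withdraw or are lost before the month-6 assessment. Month-2 conversion is then measured only in people selected for a later good response. A Kaplan-Meier curve for time to culture negativity would be shortened, and Cox estimates of its predictors would come from a set defined by a later event.

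Groups C and D are affected differently: with no randomisation, nobody in them meets the mITT definition. At stake are the descriptive response rates by regimen, which readers will take as the early efficacy of each regimen in the patients who started it.

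**Working it through.** **1. The plan's own enrolled and randomised numbers (A and B).** Inputs from Sample size calculation: favourable rate 73% in both duration arms, margin 15 points, one-sided 5%, power 80%, drop rate 20%, FR-6 rate 90%.

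- Per duration arm: n = (1.645 + 0.842)² × 2 × 0.73 × 0.27 / 0.15² = 108.3, so 109; two arms 218.
- In one step: 218 / 0.8 / 0.9 = 302.8, so 303.
- Stepwise: 109 / 0.8 = 136.25, so 137 per arm, 274 randomised; 274 / 0.9 = 304.4.

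The stated 304 per regimen is reproduced within rounding (303 to 305). The plan therefore treats FR-6 as a proportion of those enrolled, with about 304 enrolled and 274 randomised per regimen.

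**2. Who falls outside the efficacy sets.**

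- A and B: 608 × 0.10 = 60.8, about 61 participants.
- C and D: all 85 + 85 = 170.
- Together about 231 of the 778 planned (231 / 778 = 30%).

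**3. FR-6.**

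- In all enrolled A or B participants: 274 / 304 = 90%. Approximate 95% CI per regimen: 0.90 ± 1.96 × √(0.90 × 0.10 / 304) = 86.6% to 93.4%.
- In mITT: 274 / 274 = 100%, and likewise in its per-protocol subset, whatever the regimen does.

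**4. Month-2 conversion.** Let p be the rate in all treated participants and q the rate in the 10% without FR-6. The article gives neither, so both are assumptions.

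- mITT rate = (p − 0.1q) / 0.9
- Overstatement = mITT rate − p = (p − q) / 9

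| p | q = 0 | q = 25% | q = 50% | q = p |
|---|---|---|---|---|
| 60% | 66.7% (+6.7) | 63.9% (+3.9) | 61.1% (+1.1) | 60% (0) |
| 80% | 88.9% (+8.9) | 86.1% (+6.1) | 83.3% (+3.3) | 80% (0) |

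The relative inflation is at most 1 / 0.9 = 1.11, reached when nobody without FR-6 has converted by month 2. It is zero when q = p. Values of q close to p cannot be excluded, because FR-6 can also fail on drug intake or CT in someone who converted early.

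**5. Time to culture-negative status.** In the mITT set conversion is complete by month four. The Randomization section counts failure to convert only at the eighth month, so participants without FR-6 can convert between months four and eight. Those times exist in the data but not in the set. The effect is to shorten the estimated time; the article gives nothing from which to size it.

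**The case against.** The strongest reply is that the mITT sentence was meant only for the randomised comparison of 6 with 9 months. C and D are never randomised, so it can hardly be a rule for every efficacy outcome, and the sample size section already uses FR-6 as a rate among those enrolled. On this view, sets for individual secondary outcomes belong in the SAP or in supplementary Tables S2 and S7, which are not shown.

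That intention is plausible, but the text does not say it. The sentence covers efficacy outcomes without exception, and the outcomes at issue are labelled as efficacy outcomes. This is a rule that has been stated and gives a wrong result, not a detail left for later. The gap for C and D shows that the rule is badly drawn and does not rescue it. An unseen document may define another set, and if so the article's sentence needs to agree with it.

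Other objections stand, and they limit the point. A reader might go further in four ways that the document does not support:

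- **That the 90% planning figure could not be checked.** It can be: FR-6 is judged at the month-6 visit, and randomised over enrolled counts would show it.
- **That the plan compares these outcomes between the 6- and 9-month arms.** No section says so. Treatment is the same in both arms up to month 6, so such a contrast would reflect chance, but the Kaplan-Meier and Cox sentence names no arm contrast.
- **That all three outcomes always precede randomisation.** Time to culture negativity does so only within the randomised set, and C and D have no randomisation to precede.
- **That conversion is certain to be inflated.** The size rests on assumed rates and may be zero.

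**Conclusion.** The point holds for the definition of the analysis sets. FR-6 equal to 100% in A and B, against a planned 90%, follows from the wording and needs no assumption. So does the absence of an efficacy set for C and D.

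The effect on conversion is modest and assumption-bound: about 0 to 7 points at a true month-2 rate of 60%, with a relative ceiling of 1.11 if exactly 10% lack FR-6. The ceiling would be higher if part of the 20% drop occurs before month 6; the article does not give its timing.

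The primary non-inferiority comparison and the sample size are not affected by this point. It should be corrected before analysis because one secondary outcome has no meaning as specified and the correction is nearly free.

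**What to change.** Amend the Statistical analysis section (and the SAP, if it repeats the sentence) as follows:

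1. Month-2 culture conversion, time to culture-negative status and FR-6 are analysed in all enrolled participants who received at least one dose, reported by starting regimen A, B, C and D.
2. These outcomes are not used as comparisons of 6 with 9 months.
3. The randomised mITT set is kept for the A/B duration comparison on outcomes arising after month 6.
4. The text says that the mITT definition applies to A and B only, and names the efficacy set for C and D.

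The cost is wording. The scheduled visits (every two weeks for two months, then monthly to the end of treatment) already cover the period concerned. Reported response rates may be slightly less favourable, because participants without FR-6 now count.
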